### Study status

The study is ongoing and the investigators are at present analysing data.

### Participant flow

In total, we included 32 college units of 10 large and diverse technical and agricultural vocational schools; a sample of approximately 22 % of all Danish technical and agricultural vocational schools. Figure 2 shows the flow of students through the recruitment and analysis phase. The baseline survey resulted in responses from 2,329 students from four intervention schools and 3,371 students from six comparison schools, representing 73 % and 81 %, respectively, of the students assumed to be eligible. The true rate is likely to be higher because, as is typical, a number of students never started, despite enrolment on the class list, and were thus not eligible for inclusion. The majority (95 % and 97 %, respectively) who were in school on the day of data collection did respond to the questionnaire. Forty-eight students were excluded because of two or more errors identified in the data control (e.g., they reported smoking ≥ 70 cigarettes per day). The response rates for the follow-up questionnaire survey were 58 % and 52 %, respectively. The response rates of reporting the personal identification number (necessary for linkage with the education register to obtain dropout at the second follow-up) were 91 % and 88 %, respectively.

**Fig. 2 Fig2:**
[figure not shown]
Flow diagram of recruitment and participation in the Shaping the Social study

### Representativeness of the study sample

Convenience samples may be biased if the sample not fully represent the population from which it has been drawn, thus the frequencies observed in the convenience sample cannot be generalised to the larger population. Based on data from nationwide registers we can determine the representativeness of the study sample. From Statistics Denmark, we have access to population data on sex, age, prior education and ethnicity of all students entering vocational education for the period of 1.10.2011 until 30.09.2012 [47]. In total, 22511 students did entering vocational education of the technical and agricultural vocational clusters comprised the study base. Formulas proposed by Sousa et al. (2004) [48] were used to calculate the expected counts and range of average variability. Data are shown in Table 2. For example, 18311 (81.3 %) students of the research setting population were male, whereas 4703 (81.2 %) students of the study sample were male. Under a normal approximation, 95 % of the study sample’s count of males was expected to fall between 4663 to 4763. Thus, the study sample’s count of males was in the acceptable range. Overall, analysis of percentages as well as expected counts and average variability indicated that the study sample and the study base were almost identical; indicating that the study sample was representative of the population in relation to sex, age, prior education and ethnicity.

**Table 2 Tab2:** Demographic characteristics of the research setting population and the study sample, and expected sample counts

	Population of the research setting (*n* = 22511)^a^		Study sample (*n* = 5794)^b^		Expected sample counts^d^	
	n	%	n	%	n	95 % CI
Sex						
Male	18311	81.3	4703	81.2	4713.0	4662.9 − 4763.1
Female	4200	18.7	1091	18.8	1081.0	1030.9 − 1131.1
Age groups, years						
15-18	10575	47.0	2700	46.6	2719.5	2655.3 − 2783.7
19-24	8262	36.7	2130	36.8	2124.7	2062.7 − 2186.7
>24	3674	16.3	959	16.6	944.8	897.3 − 992.3
Prior education						
Completed only elementary school or less	17520	81.6	4561	80.6	4615.4	4565.7 − 4665.1
Completed an education above elementary school^c^	3954	18.4	1096	19.3	1041.6	991.9 − 1091.4
Ethnicity						
Danish origin	20019	89.8	5105	89.2	5141.5	5102.6 − 5180.4
Immigrants/descendants	2272	10.2	620	10.8	583.5	544.6 − 622.4

^a^1-10-2011 to 30-9-2012; Statistics Denmark

^b^Self-reported

^c^Vocational school, high school, or higher education

^d^Calculated by formulas proposed by Sousa et al. (2004) [47]

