### Setting

After nine compulsory years of primary and lower secondary school, almost all young people of Denmark choose to continue into the academically oriented upper secondary schools system, which is preparing students for tertiary education or into vocational education organized in separate schools spread out across large and medium sized cities. About 23% will choose vocational education [27]. Vocational education includes commercial, agricultural, technical, and social and healthcare programs leading to professions such as farmer, carpenter or web integrator. All programs are initiated by a school-based basic course lasting 20–25 weeks. The basic courses usually started four times a year and are flexible in duration depending on the student’s prior qualifications and ambitions. This means that some students within a class finish the basic course before others, and therefore a class is not a definite unit. Additionally, the high dropout rate implies that classes are merged during the basic course. We defined a class as students entering the same programme (e.g., carpenter) on the same date at the same address.

The vocational schools are organized into two levels. The upper level is the school with a management board. Next level is departments (e.g., construction) which are each headed by an inspector, one or more educational managers and an administration manager, and, typically, the departments have separate physical area and culture. In Shaping the Social, the upper analyze level will be these departments within schools (named college units).

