### Data collection

The students answered a questionnaire within the first week of their basic course (T0) and at 10-week follow-up (T1). Teachers of the classes that were involved in the intervention answered a questionnaire about implementation at 10-week follow-up. School dropout rates will be tracked via national education registers [28] through a 2-year follow-up period (T2). Table 1 presents an overview of the collected data and the study time path. All residents in Denmark have an unique and permanent personal identification number, which allows individual-level linkage between nationwide registries [29]. In the baseline and 10-week follow-up questionnaire, the students were asked for their personal identification number in order to match the responses between the data collections and to follow up on individuals in registers.

**Table 1 Tab1:** Collection of data and time path

	Instrument	Baseline	Follow-up	
		T0	T1	T2
			10 weeks	2 years
Personal characteristics				
Sex, age, ethnic origin, ethnic identity, parental education [44], family social class, distance to school, living arrangement, having children, quantitative and qualitative aspects of social relations [36], health and health behaviour [36], level of Danish reading and writing, level of prior schooling, prior academic achievement and academic self-efficacy [45]	Self-reported	X		
Primary outcomes				
Student well-being [33]	Self-reported		X	
Cigarette smoking [36]	Self-reported	X	X	
School dropout	Register data			X
Secondary outcomes				
Life satisfaction [39], physical and psychological symptoms [37], loneliness [38], alcohol consumption, use of cannabis and other illicit drugs [36]	Self-reported	X	X	
Immediate outcomes				
Indicators of well-conducted introduction period	Self-reported	X	X	
Indicators of classroom management [33]				
Degree of implementation				
Preliminary meeting at the school with a specialist teacher, the students and their relatives	Teacher reported		X	
Welcoming activities at first school day	Teacher reported		X	
Timetable with a clear description of course, time and clothing requirements	Teacher reported		X	
Class meeting every morning including beverages or food	Teacher reported		X	
Scheduled breaks	Teacher reported		X	
Created a place for hanging out during breaks	Teacher reported		X	
Monthly events during school hours organised across sections, and followed by an open café	Teacher reported		X	

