Access to school facilities outside school hours and a member of staff is present	Teacher reported		X	

We developed the student questionnaires with items based on Danish population surveys, and on validated scales when possible. The questionnaires were subject to an expert hearing followed by pilot testing among students (*n* = 117) in three vocational schools (not included in the intervention study). Self-developed items, especially, were giving attention. We kept the questionnaires as short as possible in order to increase the response rate [30].

Data collections were performed during class and took approximately 20 min. Baseline assessment was not possible before school start, because school records of students were incomplete. Moreover, we chose to collect data during school time because the student population included socio-demographically diverse subgroups and a predominately male and young population, which are characteristics that can predict non-response [31, 32]. Questionnaires were web-based with an audio voice-over so the students heard questions through headphones while they appeared on screen. Follow-up of non-respondents in the 10-week-follow-up assessment was by electronic mail, mobile text message and a mailed letter.

Baseline data collection started in October 2011 and ended in October 2012, and comprised five samples of basic courses (autumn 2011, winter 2012, spring 2012, summer 2012 and autumn 2012).

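### Table 2 compares a five-intake sample of unreconciled size with a 12-month register population, and the text declares prior education representative although both counts lie outside the table's own ranges

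*Protocol article*

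**What the plan says.** Under Data collection, the protocol article states: "Baseline data collection started in October 2011 and ended in October 2012, and comprised five samples of basic courses". The samples are listed as autumn 2011, winter, spring and summer 2012, and autumn 2012. The same section places the baseline questionnaire in the first week of the basic course. Under Setting it adds: "The basic courses usually started four times a year".

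Under Representativeness of the study sample, the reference data cover "all students entering vocational education for the period of 1.10.2011 until 30.09.2012", and the size is given thus: "In total, 22511 students did entering vocational education of the technical and agricultural vocational clusters". Table 2 sets these entrants beside a study sample of 5,794, with an expected count and a 95% range for each category. The text uses the range as an acceptance rule: the male count is called acceptable because it lies inside. It then concludes that the sample is representative on sex, age, prior education and ethnicity.

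Under Participant flow: "The baseline survey resulted in responses from 2,329 students from four intervention schools and 3,371 students from six comparison schools". The abstract gives the same two figures. Forty-eight students are reported as excluded in data control.

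**The concern.** Determining representativeness is a stated aim of the article (end of the Background). Study strengths and limitations then cites the result when it discusses selection bias from non-random allocation. The check should therefore hold on its own terms. Three things stand in the way:

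- **Window.** Students first surveyed during October 2012, in their first course week, are compared with a population that closes on 30 September 2012. With about four starts a year, five intakes do not fit into one yearly cycle.
- **Sample size.** The n in Table 2 is not the number of baseline respondents reported elsewhere.
- **Conclusion.** One of the four variables fails the acceptance rule that the text applies to sex, and the conclusion does not say so.

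**Working it through.** **Inputs.** All come from Table 2 unless stated. Sex: N = 22,511, of whom 18,311 male; n = 5,794, of whom 4,703 male. Prior education (non-missing totals): N = 17,520 + 3,954 = 21,474; n = 4,561 + 1,096 = 5,657. Respondents by arm and exclusions come from Participant flow.

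**1. Reproducing the stated range.** Take p = K/N, expected count np, and range np ± 1.96·√[np(1−p)·(N−n)/(N−1)].
- Males: p = 18,311/22,511 = 0.8134 and np = 4,713.0. The half-width is 50.1, giving 4,662.9 to 4,763.1. This is exactly the table's figure.
- Without the factor (N−n)/(N−1), the half-width is 58.1 and the range 4,654.9 to 4,771.1, which does not match.
- The age and ethnicity ranges reproduce to within 0.2 of a count. Prior education (elementary school only) reproduces to within 0.7: 4,566.3 to 4,664.4, against 4,565.7 to 4,665.1 in the table.

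The arithmetic is therefore sound, and it treats the sample as a simple random subset of the register population.

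**2. Effect of the window.** Let a share s of the sample lie outside the register window, with the same p. With n₁ = n(1−s), the variance is n₁p(1−p)(N−n₁)/(N−1) + (n−n₁)p(1−p). The article does not give s, so a range is shown.

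| Share outside (assumed) | Males (observed 4,703) | Elementary only (observed 4,561) |
|---|---|---|
| 0% | 4,662.9–4,763.1, inside | 4,566.3–4,664.4, outside |
| 10% | 4,661.3–4,764.7, inside | 4,564.7–4,666.1, outside |
| 20% | 4,659.9–4,766.1, inside | 4,563.3–4,667.5, outside |
| 40% | 4,657.6–4,768.3, inside | 4,561.0–4,669.7, on the limit |
| No correction (limit) | 4,654.9–4,771.1, inside | 4,558.2–4,672.5, inside |

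The male half-width grows from 50.1 to 53.1 at 20% (53.1/50.1 = 1.06) and to 58.1 at the limit (58.1/50.1 = 1.16). All age and ethnicity counts stay inside throughout. For example, the Danish-origin count of 5,105 lies inside both 5,102.8–5,180.2 (full correction) and 5,096.6–5,186.4 (none).

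**3. Sample size.** 2,329 + 3,371 = 5,700, and 5,794 − 5,700 = 94. Adding back the exclusions gives 5,700 + 48 = 5,748, which is still 46 short. The two sex counts sum to 4,703 + 1,091 = 5,794, so the column heading is not a misprint.

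**4. Prior education against the article's own ranges.** Elementary only: 4,561 is below 4,565.7. Above elementary: 1,096 is above 1,091.4. With the correction, z is about 2.17 in absolute value; without it, 1.87. The percentages are 80.6 in the sample and 81.6 in the population.

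**The case against.** The best defence is that nothing here is miscalculated and little turns on it. The ranges reproduce from the stated n and N. Widening them makes the sample look more compatible with the population, which favours the article. The percentages are close on every variable, and the text relies on them as well as on the ranges. The article gives no intake sizes, start dates or exact closing day, so the share outside the window could be small. The flow diagram was not available and may account for 5,794. Table 2 enters no effect estimate, and the article separately says that unbalanced student characteristics will be examined and possibly controlled for.

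Most of this stands, and it rules out several stronger readings that a reader might infer:

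- **That the ranges are wrong.** They are right for their inputs. Only the assumption that every sampled student belongs to the 22,511 is contradicted.
- **That one fifth of the sample is outside the window.** This needs five equal intakes and an autumn 2012 intake that began entirely after 30 September. It is an upper-end assumption.
- **That the correction decides the prior-education row.** At 20% outside, the row still fails. It passes only when roughly 40% or more is outside, or with no correction at all.
- **That the second autumn biases the comparison.** The two autumn intakes are different cohorts, and nothing in the article shows that age or prior education varies by season.

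The defence does not reach the last point of the check. On prior education, the conclusion disagrees with the table that supports it.

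**Conclusion.** The point holds, with a modest numerical effect. The sample and reference windows do not coincide, and the ranges are slightly too narrow: about 6% on the assumption of one fifth outside, and 16% at most. No verdict for sex, age or ethnicity changes under any assumption tried. The gap between 5,794 and 5,700 is 94 students (94/5,794 = 1.6%). It is a query to be reconciled and does not show that the wrong students were used.

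The substantive error is in the text. Prior education lies outside the article's own ranges, remains outside under every assumed share below about 40%, and is nevertheless declared representative. A reader might go further and infer that the sample is unrepresentative on prior education. The documents do not support that either: the difference is one percentage point, and the ranges treat students as drawn individually although the sample came in classes within ten schools. What the documents show is a conclusion that does not follow from the rule the article applies. The sensitivity figures assume the same category proportions inside and outside the window.

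**What to change.** 1. State how 5,794 arises from the 5,700 baseline respondents, or rerun Table 2 on the 5,700.
2. Restrict the sample column to students who started between 1 October 2011 and 30 September 2012, or extend the register population to the last included start date.
3. Apply the finite-population correction only to students inside the register window.
4. Restate the conclusion row by row. On the present figures, sex, age and ethnicity lie within their ranges, while prior education differs slightly (80.6% against 81.6% with elementary school only) and lies outside its range. Carry this wording into Study strengths and limitations.

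The cost is one repeated descriptive table and, if the window is extended, about one more month of aggregate register counts. Trial conduct and the effect analysis are not touched.

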### Sample size

Sample-size calculation was performed to determine the number of classes needed in order to be able to detect a difference between the intervention and comparison group with respect to student well-being, smoking and school dropout [46]. From a nationwide student satisfaction survey in 2010 at Danish vocational schools, we selected measures on daily smoking (yes, no), consideration of dropping out (yes, no), and two indicators on student well-being: solidarity among students (yes, no), and a positive welcoming atmosphere created by the school (yes, no). Overall, 41 % were daily smokers, 19 % considered dropping out, 17 % reported a lack of student solidarity, and 21 % reported a lack of a positive welcoming atmosphere. We estimated the intra-class correlation to 0.006 for welcoming atmosphere, 0.05 for student solidarity and smoking, and 0.016 for dropout considerations. With a desired power of 80 %, a 5 % significance level, a two-sided test, and an expected 20 % reduction for each outcome in the intervention group, the minimum number of classes in intervention and comparison groups was calculated as ranging from 60 to 110. To be conservative, we chose the highest number of clusters (i.e., classes, *n* = 110). Another necessary assumption for the power calculation was that each class had an average of 20 students. Allowing for 20 % non-respondents, a total of about 5,280 students needed to be included.

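### Table 2's 95 % ranges assume students sampled individually at random, which this school-based sample was not, and the prior-education counts fall outside them although representativeness is declared

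*Protocol article*

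**What the plan says.** The article's Background names representativeness as an aim. The section Representativeness of the study sample compares the survey sample with register data: "In total, 22511 students did entering vocational education of the technical and agricultural vocational clusters comprised the study base". For sex it reports that "18311 (81.3 %) students of the research setting population were male, whereas 4703 (81.2 %) students of the study sample were male", and it then gives the reference range: "Under a normal approximation, 95 % of the study sample’s count of males was expected to fall between 4663 to 4763". The male count is judged acceptable because it lies inside. Table 2 prints such a range, headed as a 95 % CI, for nine categories of sex, age, prior education and ethnicity. The section concludes that "analysis of percentages as well as expected counts and average variability indicated that the study sample and the study base were almost identical" and that the sample is representative on all four characteristics.

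The sampling is described elsewhere. Study design says that the four intervention schools were a convenience sample. The comparison schools were picked from 16 eligible schools for geographic diversity and then by willingness to take part. Participant flow says: "In total, we included 32 college units of 10 large and diverse technical and agricultural vocational schools". Baseline response was 73 % and 81 % of students assumed eligible. Sample size recognises that students within classes are alike: "We estimated the intra-class correlation to 0.006 for welcoming atmosphere, 0.05 for student solidarity and smoking, and 0.016 for dropout considerations".

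Study strengths and limitations then cites the representativeness result directly after naming selection bias from the lack of random allocation.

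**The concern.** A 95 % range for a sample count has meaning only relative to a sampling scheme. The article calls the sample a convenience sample, selects schools rather than students, defines classes by trade, and plans multilevel models for the effect analyses. If the Table 2 ranges ignore all of this, their coverage label is wrong and falling inside or outside them is not the test that the text takes it to be.

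Two things are at stake: a stated aim of the article, and the later use of the result as reassurance about selection bias. There is also a plain question of consistency, namely whether every count lies inside its own printed range, as the conclusion implies.

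**Working it through.** **1. Reproduce the printed range.** Inputs from Table 2: N = 22,511, register males 18,311, n = 5,794.

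- p = 18,311/22,511 = 0.8134; expected males = n·p = 4713.0.
- Individual random sampling without replacement: SD = sqrt(n·p·(1−p)·(1−n/N)) = 25.55.
- Range: 4713.0 ± 1.96 × 25.55 = 4662.9 to 4763.1, equal to the printed range to the decimal.
- Without the finite-population factor the range is 4654.9 to 4771.1, which does not match.

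The factor sqrt(1 − 5,794/22,511) = 0.86 narrows the range by 14 %. The other rows reproduce to within 0.7 of a count. The ranges therefore assume individual random sampling, with no clustering.

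**2. Allow for clustering.** The article gives no intra-class correlation (ICC) for the four demographic characteristics. As an assumption, its planning values of 0.006 to 0.05 are applied at three levels. The design effect is 1 + (m − 1)·ICC for clusters of m students, and the half-width of 50.1 is multiplied by its square root. Class size 20 is from Sample size; the other sizes are 5,794/32 = 181 and 5,794/10 = 579.

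| Clustering level | m | Design effect | Half-width factor | Male half-width |
|---|---|---|---|---|
| As printed | – | 1 | 1 | 50 |
| Class | 20 | 1.11 to 1.95 | 1.06 to 1.4 | 53 to 70 |
| College unit | 181 | 2.1 to 10.0 | 1.4 to 3.2 | 72 to 158 |
| School | 579 | 4.5 to 29.9 | 2.1 to 5.5 | 106 to 274 |

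For males this gives 4643 to 4783 at class level with ICC 0.05, and 4607 to 4819 at school level with ICC 0.006.

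**3. Compare each count with its printed range.** Seven of nine lie inside. The two that do not are the prior-education rows:

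- "Completed only elementary school or less": observed 4,561, printed range 4565.7 to 4665.1, so below.
- Education above elementary school: observed 1,096, printed range 991.9 to 1091.4, so above.

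These are the two halves of one split, so this is one departure, about 2.17 SD on the article's own assumption. With clustering at college-unit or school level, 4,561 is inside for every ICC tried (for example 4513 to 4718 at school level with 0.006). With clustering in classes only, it is inside at 0.016 (4559 to 4671) and 0.05 (4547 to 4684), but still outside at 0.006 (4564 to 4667).

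**4. Compare the percentages.** Register against sample:

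- male: 81.3 and 81.2
- ages 15–18: 47.0 and 46.6
- ages 19–24: 36.7 and 36.8
- over 24: 16.3 and 16.6
- elementary school or less: 81.6 and 80.6
- Danish origin: 89.8 and 89.2

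The largest gap is prior education, where the standardised difference is (0.8159 − 0.8063)/sqrt((0.8159 × 0.1841 + 0.8063 × 0.1937)/2) = 0.0096/0.391 = about 0.025. Ethnicity is about 0.02, and sex and age are smaller.

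**The case against.** The best defence has four parts.

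- **Direction.** Ranges that are too narrow make the check stricter. Widening them moves no in-range count outside. A reader might infer that the narrow ranges produced the favourable verdict; they did not.
- **The percentages carry the conclusion too.** The text cites percentages as well as expected counts, and the percentages really are close.
- **Size.** A reader might infer that the ranges are shown to be far too narrow. The article does not support that. Its ICCs are for other items, in a calculation whose clusters are classes of 20. At that level the understatement is at most about 1.4-fold. The larger factors come from moving those ICCs to college units or schools. That is plausible, since Setting describes departments as typically having separate areas and cultures, but it is not documented for these characteristics.
- **No interval is strictly valid.** The schools were not randomly selected either, so a school-clustered range would also rest on an untrue sampling model.

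All four points stand and they limit the finding. They do not rescue the 95 % label, which is attached to a scheme that was not used. Nor do they answer the prior-education rows, where the article's own criterion is not met and the text does not say so.

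**Conclusion.** The point holds in limited form. The Table 2 ranges are those for individual random sampling, as the exact reproduction shows, and their 95 % coverage does not apply to respondents in selected courses at 10 purposively chosen schools. They understate variability by a factor between 1.06 and 5.5, depending on the level of clustering and on borrowed ICCs; the true demographic ICCs are not reported.

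Read at face value, the ranges contradict the declared representativeness on prior education. Read with college-unit or school-level clustering, prior education is inside, but being inside then says less. On either reading the ranges do not support the conclusion as an inferential statement. What is supported is descriptive: the percentages are within about one point of the register on four characteristics.

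It does not follow that the sample is unrepresentative. A count outside a range with the wrong coverage is weak evidence, and a one-point gap is small.

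Agreement of the pooled sample with the register also cannot answer selection bias between the arms, because opposite departures in the two arms can cancel in the total. The planned effect analyses, which model students within classes within college units, are unaffected.

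**What to change.** - In Table 2, drop the expected-count ranges as the criterion, or label them as valid only under individual random sampling.
- Report register and sample percentages with absolute or standardised differences. School-clustered intervals may be added, with the caveat that the schools were not randomly chosen.
- Reword the conclusion to say that the observed percentages are close to the register figures on four characteristics.
- If the ranges are kept, state that prior education lies outside its range.
- In Study strengths and limitations, do not offer this result as an offset to selection bias between the arms.

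The cost is one revised table and a few sentences, plus one re-run if clustered intervals are wanted. The price is wider intervals or none, and a less emphatic claim.
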